### Data and sample collection

We will use the Chinese Clinical Research Public Management Platform (Res Man) to collect and manage the data. The experimental data can only be accessed and manipulated by the research team.

The person in charge of the project will have access to the real-time data, but cannot make any changes to the data.

All data collectors will receive uniform training to ensure that data collected through questionnaires will have high quality and consistency. The Short-Form Health Survey 36 (SF-36) [29], designed to assess the quality of life through a comprehensive assessment of physical, mental, and social components and COOP/WONCA charts, will be completed at baseline, immediately after the final treatment, and then at 12 weeks and 24 weeks after the final treatment. A pulmonologist will collect data on pulmonary function from all subjects to ensure consistency prior to and following the final treatment, as well as 24 weeks after the final treatment. We also will examine the follow-up records for each patient regarding respiratory and cardiovascular diseases at 12 weeks and 24 weeks following treatment. The time frame for data collection and assessments is shown in Fig. 2.

**Fig. 2 Fig2:**
[figure not shown]
Participant timeline

The number of TH1 and TH2 cells in the peripheral blood of subjects and the TH1/TH2 ratio will be measured at the time of enrollment (baseline) and again following treatment (8 weeks later). Similarly, we will determine the TH1/TH2 polarization state, including the concentrations of serum interferon-γ (IFN-γ), interleukin-4 (IL-4), interleukin-12 (IL-12), interleukin-6 (IL-6), interleukin-8 (IL-8), and intercellular adhesion molecule-1 (ICAM-1), as well as liver and renal function to assess drug safety, at baseline and following treatment.

The concentrations of TH1 and TH2 cells in the peripheral blood immune cell population will be detected by flow cytometry using a CytoFLEX Flow Cytometer (Beckman Coulter, Brea, CA, USA). Serum IFN-γ, IL-4, IL-12, IL-6, IL-8, and ICAM-1 levels will be measured using commercially available enzyme-linked immunosorbent assay (ELISA) kits. The nurse will collect the venous blood of the subjects, some will be stored in a 4 °C ice pack and immediately sent to the laboratory for testing (liver function and renal function), some will be stored at room temperature and sent to the laboratory for flow cytometry testing, and a part was frozen at −80 °C for ELISA detection. All blood samples will be assessed in the Laboratory of Hospital of Chengdu University of Traditional Chinese Medicine. The blood products of all subjects will be destroyed uniformly after the end of the study.

### Outcome measures

#### Primary outcome measure

At enrollment and 8 weeks later, we will evaluate the concentrations of cells about TH1 and TH2 in peripheral blood and the TH1/TH2 polarization state (IFN-γ, IL-4, IL-12, and IL-6) and calculate the TH1/TH2 ratio using the IFN-γ/IL-4 balance index. We will examine the difference in the concentration of TH1 and TH2 cells in the peripheral blood and the TH1/TH2 polarization state between the treatment group and the placebo group.

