**Methods:**

This study was designed as a prospective, randomized, double-blinded (to participants and researchers), placebo-controlled clinical trial. The research plan is to randomly select 120 eligible adults based on the difference in PM2.5 exposure in the Chengdu subway station. They should be aged 20–65 years old and work in the subway station more than or equal to 3 times a week, each time greater than or equal to 8 h, and had worked continuously in the subway station for more than 2 years. All participants will receive omega-3 fatty acids or placebo for 8 weeks. The primary outcomes will be changes in the TH1/TH2 cell polarization index and changes in serum cytokine concentrations. Secondary outcomes will be changes in early indicators of atherosclerosis, pulmonary function, COOP/WONCA charts, and scores on the Short-Form 36 Health Survey for quality of life. Results will be analyzed to evaluate differences in clinical efficacy between the two groups. A 6-month follow-up period will be used to assess the long-term value of omega-3 fatty acids for respiratory and cardiovascular disease endpoints.

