### Sample size

G*Power 3.1 will be used to calculate the sample size necessary to have sufficient statistical power [26]. The sample size calculation will be based on a previous study of omega-3 fatty acids and their effects on up-regulating the TH1/TH2 ratio by ~ 32.5% [27]. The type I error is 0.05 and the power is 80%. Considering a dropout rate of 20%, we aim to recruit 120 subjects. The treatment group and the placebo group were assigned 60 participants each. Based on the grouping of our experiment, we will be divided into the high exposure group and low exposure group according to PM2.5 exposure. In the high and low exposure groups, 30 subjects were treated with omega-3 fatty acids and placebo.

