### Statistical methods

IBM SPSS Statistics V.25 software will be used for statistical analysis of the data collected in this study. Subjects who withdrew from the experiment but received at least one treatment will still be included in the intention-to-treat analysis. We will use various attribution methods to conduct sensitivity analysis to test whether the results are reliable for different assumptions about missing data. Demographic and baseline data will be tabulated and evaluated using analysis of variance (ANOVA) or the *χ*^2^ test. Analysis of variance was performed on categorical variables, and the Pearson *χ*^2^ test was performed on continuous variables. Subgroup analyses will be performed according to the subjects’ working years (2–6 years, 6–10 years, and over 10 years) and average working hours per week (24–36 h and over 36 h). If conditions are appropriate, subgroup analysis will be performed with reference to the above criteria. 95% CI will be used for continuous variables. In this study, all statistical tests will be two-way, and a *P* value < 0.05 is considered valid.

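### Seven unranked primary quantities share one two-sided 0.05 threshold, so the 0.05 in the sample size section covers one test, the TH1/TH2 ratio, and not the primary family

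*Protocol article*

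**What the plan says.** - **Primary outcome measure** (heading in the singular): at enrolment and at 8 weeks the trial will "evaluate the concentrations of cells about TH1 and TH2 in peripheral blood and the TH1/TH2 polarization state (IFN-γ, IL-4, IL-12, and IL-6"). The same sentence then adds a derived quantity: "calculate the TH1/TH2 ratio using the IFN-γ/IL-4 balance index". The comparison between arms follows: "We will examine the difference in the concentration of TH1 and TH2 cells in the peripheral blood and the TH1/TH2 polarization state". No order or priority is given.
- **Abstract, Methods**: "The primary outcomes will be changes in the TH1/TH2 cell polarization index and changes in serum cytokine concentrations". The plural is used here, and the index and the cytokines have equal standing.
- **Sample size**: based on one variable, citing an earlier study of omega-3 "up-regulating the TH1/TH2 ratio by ~ 32.5"%. Its error rates are given next: "The type I error is 0.05 and the power is 80"%. With 20% dropout the total is 120, 60 per arm.
- **Statistical methods**: "In this study, all statistical tests will be two-way". The threshold is set once for every test: a P "value < 0.05 is considered valid". The section mentions no adjustment, test order or rule for combining primary results.
- **Data and sample collection**: a TH1/TH2 ratio is listed with the TH1 and TH2 cell numbers in blood. The serum cytokines come in a separate sentence.

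**The concern.** The trial is sized and its alpha set for one comparison, but seven quantities carry the primary label: TH1 cells, TH2 cells, IFN-γ, IL-4, IL-12, IL-6 and the IFN-γ/IL-4 ratio. Nothing says which of them decides whether the trial is positive. A report that followed the article as written could present any one nominally significant result as the primary finding.

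This matters because the abstract expects the trial to support promoting omega-3 in clinical practice. The Intervention section also makes post-trial supply to the control participants depend on omega-3 proving beneficial, without naming the outcome that settles it.

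**Working it through.** **1. Count of the family.** Cells: TH1, TH2 (2). Cytokines: IFN-γ, IL-4, IL-12, IL-6 (4). Ratio: IFN-γ/IL-4 (1). Total 7. If the ratio listed with the cell counts under Data and sample collection is a separate cell-count ratio, the total is 8.

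**2. The stated figure.** The article gives a type I error of 0.05 for the calculation on the TH1/TH2 ratio. With k = 1 test, 1 − 0.95^1 = 0.05, so it holds for that test.

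**3. Ceiling for the family.** Suppose that every quantity is tested at two-sided 0.05, that there is no treatment effect on any of them, and that one significant result is enough:

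- k = 6 (without a ratio): 1 − 0.95^6 = 26.5%
- k = 7: 1 − 0.95^7 = 30.2%
- k = 8: 1 − 0.95^8 = 33.7%

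These are the values under independence. By Šidák's inequality they are also upper limits for jointly normal two-sided test statistics, whatever the correlation.

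**4. A more realistic value.** The seventh quantity is calculated from two of the others, so seven independent tests are not a natural model. Six correlated standard normal statistics were simulated under the null hypothesis, with the seventh set to the standardised difference of the first two (a log-ratio with equal SDs). The common correlation is an assumption, because the article gives none.

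| Common correlation | Chance of at least one P < 0.05 |
|---|---|
| 0 | 28% |
| 0.3 | 26% |
| 0.5 | 24% |
| 0.7 | 20% |
| 0.9 | 15% |

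**5. Cost of keeping all seven.** Bonferroni gives 0.05/7 = 0.0071 per test. The article states no SD, so the standardised effect must be inferred:

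- Evaluable per arm after 20% dropout: 60 × 0.8 = 48 (assumption).
- Effect giving 80% power at two-sided 0.05 in a t-test with 48 per arm: d ≈ 0.58.
- Power at the same d and n with alpha 0.0071: about 53%.
- To regain 80%: about 77 evaluable per arm, that is 2 × 77 / 0.8 = 192.5, or 193 in total against 120 planned.

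Steps 3 and 4 do not depend on this inferred effect.

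**The case against.** **The 0.05 was never a family-wise promise.** It is an input to a calculation on one variable, and it is correct for that variable. This stands. A reader might infer that the design guarantees 0.05 across its primary outcomes and breaks the guarantee, but the text makes no such promise. What it lacks is a statement of which primary quantity that 0.05 belongs to.

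**Multiplicity is often left to the full protocol or an analysis plan.** This stands in part. An adjustment could exist in a document not shown, and a threshold of 0.05 is compatible with adjusted P values. But the choice of primary outcome belongs in the protocol. This article affirmatively gives several outcomes that status and sets one threshold for every test. A later plan would have to amend that, not merely add detail.

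**A false-positive rate of 30% needs a rule that the article does not contain.** This stands. A reader might infer that the trial has a 30% chance of a false-positive primary result. The documents do not support that: they neither state nor exclude that one significant quantity is enough, and the derived ratio pulls the figure below the ceiling.

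**There are signs of a lead variable.** The sample size uses the ratio, the abstract names the index first, and the Discussion calls the polarization state the main variable. These are hints and not a declaration. The outcome section describes that state by four cytokines, so the Discussion's phrase does not pick out one quantity.

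**Conclusion.** The concern holds in a bounded form. The article makes seven quantities primary without ranking them and applies two-sided 0.05 to all tests. Its stated alpha therefore controls error for one test of the TH1/TH2 ratio and not for the primary family.

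If any one significant quantity may be claimed as success, the family-wise error is about 15% to 28% under the log-ratio model, for common correlations from 0.9 down to 0. Thirty per cent is the ceiling for seven tests, and 34% for eight. These figures assume that there is no effect on any marker, approximately normal test statistics and no adjustment. The fall in power from 80% to about 53% under Bonferroni rests further on 48 evaluable participants per arm and d of about 0.58, neither of which the article states.

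A related ambiguity bears on the remedy. The TH1/TH2 ratio could be the ratio of flow-cytometry cell counts or the serum IFN-γ/IL-4 index, and Sample size does not say which was used.

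**What to change.** In Primary outcome measure and in the abstract, name one TH1/TH2 ratio as the sole primary outcome, tested between arms at two-sided 0.05. State whether it is the flow-cytometry cell ratio or the serum IFN-γ/IL-4 index. Say the same in Sample size, so that the variable sized and the variable tested are one. Naming the TH1/TH2 ratio without this leaves two candidates from different assays.

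Make the other ratio, the two cell counts and the four cytokines secondary. Either adjust them by Holm's method, or report them with 95% confidence intervals and no confirmatory claim.

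Make the change before unblinding and record that it was made without knowledge of results. This matters because Trial status expected completion around July 31, 2021, before the article appeared in February 2022. It has to go through the route in Modification of the protocol: agreement of the project leader and the supervisor, with the team and the ethics committee notified first.

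The cost is a formal amendment and the loss of confirmatory status for the other markers. The planned 120 participants need not change, provided that the ratio named is the one that was sized.

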### Randomization, allocation, and concealment

Before the subjects agree to participate in this study, all qualified subjects who satisfy the inclusion and exclusion criteria will be given an information sheet describing the study and an opportunity to ask questions and clarify their concerns with the investigators. During the study, both the participants and the researchers will be blinded to the grouping information for each subject based on the PM2.5 exposure level. According to the difference in PM2.5 exposure, 120 random numbers will be generated by BMISPSSStatistics24.0 software, and 60 random numbers will be allocated to the PM2.5 high-exposure group and PM2.5 low-exposure group (stratified random). The researcher in charge of blinding will use two opaque envelopes to seal the random numbers and will carefully check whether the serial numbers and drug numbers on the cover and letterhead are consistent with the labels on the drug packaging. Each subject will be provided with a corresponding emergency envelope. In case of an event threatening the safety of the subject, the researcher will allow the unblinding in an emergency after the evaluation so that the patient can be properly treated. In an emergency, an independent pharmacist will open the sealed envelope and notify the investigator of the assignment. Information about the date, time, and reason to remove blindness will be entered in clinical case forms (CRFs) and envelopes.

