### Intervention

We plan to recruit 120 subjects who will be automatically divided into two groups based on their PM2.5 exposure level in the work environment: high PM2.5 exposure group (*n* = 60) and low PM2.5 exposure group (*n* = 60). In the high-exposure group, 30 people will receive omega-3 fatty acid treatment and the other 30 subjects will receive placebo treatment. Participants in the low-exposure group will receive an identical treatment regimen.

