Intervention group: Participants will receive treatment from the same batch of omega-3 fatty acids (1200 mg/capsule) provided by Kirkland, Canada. Participants will take two capsules every morning for 8 weeks and will be followed for 24 weeks after the trial. The omega-3 fatty acid capsules will be stored in a dry environment at room temperature.Placebo group: Participants will receive placebo treatment, containing soybean oil as the main ingredient, which has been produced by the Placebo Experimental Center of the School of Pharmacy, Chengdu University of Traditional Chinese Medicine. The physical appearance and weight of the placebo will be the same as the omega-3 fatty acid capsules, and the administration methods, experimental period, and storage methods will be identical to those in the intervention group.The capsules for the intervention group and the placebo group will be packaged in the same box. Each box will contain 8 weeks of drug dosage and will include the name of the subject, dosage, consumption schedule, description of storage conditions, and expiration date. “Experiment only” will be highlighted in a prominent position on the box. We have selected soybean oil as the placebo (comparison) agent because it is commonly used in daily cooking, its physical properties are similar to omega-3 fatty acids and it has no obvious effects on TH1/TH2 polarization [28].The drug to be used in this project is a nutritional supplement with controllable safety risks. The participant may do so if he/she has no adverse events or side effects. However, if the subject has diarrhea or nausea, their participation in the trial may be suspended and the adverse event will be reported to the research team. Due to the special nature of omega-3 fatty acids, we will prohibit participants from using antioxidant supplements, such as vitamin E, during the trial. Medications used by participants to treat other diseases will not be curtailed or changed. If omega-3 fatty acids are beneficial to subjects with high PM2.5 exposure, we will put the control subjects on the “waiting list,” that is, after the trial, the control subjects will also be provided with omega-3 fatty acids for 8 weeks free of charge.

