#### Secondary outcome measures

We will evaluate the difference in secondary indicators between the treatment group and the placebo group from the following four aspects.
A pulmonary function test will be performed to evaluate the impact of PM2.5 on lung function in each subject (baseline, end of treatment, and 24 weeks).Early indicators of atherosclerosis, including IL-8 and ICAM-1, will be measured (baseline and end of treatment).The SF-36 questionnaire will be used to assess the health status of each subject and to generate a COOP/WONCA chart. The quality of life will be summarized for eight aspects: physical functioning, physical role functioning, physical pain, general health, vitality, social functioning, emotional health, and mental health (baseline, end of treatment, 12 weeks, and 24 weeks).Safety and adverse reactions to drug treatment will be monitored.

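### No stated analysis gives the treatment effect in highly exposed workers, although the title, the stratified randomization and the post-trial offer all turn on PM2.5 exposure

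*Protocol article*

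**What the plan says.** **Exposure is a design factor.** Under Randomization, allocation, and concealment, the random numbers are split by exposure level: "60 random numbers will be allocated to the PM2.5 high-exposure group and PM2.5 low-exposure group (stratified random"). The Intervention section gives the layout inside a stratum: "In the high-exposure group, 30 people will receive omega-3 fatty acid treatment and the other 30 subjects will receive placebo treatment". The low-exposure group is treated in the same way. By the inclusion criteria, that group consists of office staff whose air-conditioning has PM2.5 filters.

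**The conclusion is drawn for high exposure.** The title names individuals with high exposure, and the Abstract's discussion looks to evidence for protecting the highly exposed. The Intervention section makes the later offer of omega-3 to controls depend on a condition: "If omega-3 fatty acids are beneficial to subjects with high PM2.5 exposure". The last paragraphs of the Background state the aim more broadly, for subway workers exposed to PM2.5.

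**The comparison is by arm only.** The primary outcome section examines cell concentrations and the "polarization state between the treatment group and the placebo group". The secondary outcome section examines the "difference in secondary indicators between the treatment group and the placebo group". The Sample size section says what those groups are: "The treatment group and the placebo group were assigned 60 participants each".

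**The subgroups omit exposure.** In Statistical methods, "Subgroup analyses will be performed according to" introduces two factors only, working years (2–6, 6–10, over 10) and average weekly hours (24–36, over 36). A further conditional sentence on subgroups points back to those same criteria.

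**The concern.** The factor that defines the trial's population of interest appears in the design and in the conclusion, but in no stated analysis between them. A treatment-versus-placebo contrast over both strata estimates an average over station-hall workers and office workers. That average can mislead about the highly exposed in two ways. A positive overall result could come mainly from the low-exposure half and still be reported as protection of highly exposed people. A null overall result could hide a benefit confined to the high-exposure half, because such a benefit is diluted by half in the average.

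The post-trial condition is the sharpest case. It asks whether highly exposed subjects benefit, and nothing stated in the article answers that. If the population behind the main claim is settled only once results are known, the protection of prespecification is lost at the point where the article makes its principal claim.

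**Working it through.** **1. Who is in the compared groups.** Sample size and Intervention give four cells of 30 (high/omega-3, high/placebo, low/omega-3, low/placebo). Each arm is 30 + 30 = 60, which matches the 60 per arm stated in Sample size. The article never uses the word pooled, but a comparison of arms of 60 necessarily combines both strata.

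**2. Is exposure analysed anywhere?** The primary comparison is by arm. So is the secondary comparison. The subgroups are working years and weekly hours, and the conditional subgroup sentence refers to the same two. No section states a within-stratum contrast, an exposure term or a treatment-by-exposure interaction. This step needs no arithmetic, and the point rests on it.

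**3. The plan's sample size.** Inputs from Sample size: type I error 0.05, power 80%, dropout 20%, a rise of about 32.5% in the TH1/TH2 ratio, N = 120. Tests are two-sided (Statistical methods). No SD or standardized effect is given, so 120 cannot be reproduced from the stated inputs. Working backwards with a two-sample t-test:
- Evaluable: 120 × (1 − 0.20) = 96, which is 48 per arm overall and 24 per arm in each stratum.
- Reading A, 120 sized for the overall comparison: 80% power at 48 per arm implies d = 0.578, an SD of 32.5/0.578 ≈ 56 percentage points. (Dividing by 1.2 instead gives 50 per arm and d = 0.566, which changes little.)
- Reading B, 60 sized for each stratum: 80% power at 24 per arm implies d = 0.826, an SD of 32.5/0.826 ≈ 39.

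The article does not say which reading applies.

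**4. Power under each reading.** If only the high stratum benefits, the overall effect is (d + 0)/2.

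| | Reading A | Reading B |
|---|---|---|
| Effect in high stratum (d) | 0.578 | 0.826 |
| Power, high stratum alone, 24 per arm | 50% | 80% |
| Overall effect if benefit is confined to high stratum | 0.289 | 0.413 |
| Power, overall test, 48 per arm | 29% | 52% |

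Over a range of assumed SDs for the 32.5-point effect, power in the high stratum alone is 79% at SD 40, 60% at SD 50, 50% at SD 56, 45% at SD 60 and 28% at SD 80.

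**5. Precision (in SD units, independent of the assumed effect).** The 95% CI half-width is t × √(2/n per arm).
- Overall: t(94) × √(2/48) = 1.986 × 0.204 = 0.41 SD.
- High stratum: t(46) × √(2/24) = 2.013 × 0.289 = 0.58 SD.

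**6. Interaction.** The difference between the two stratum effects has variance 4/24 in SD² units. Under Reading A, with benefit confined to the high stratum, the interaction test also has about 29% power (normal approximation).

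**7. Working-years bands.** The bands 2–6 and 6–10 both include exactly 6 years, so a person with 6 years' service has two possible categories.

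**The case against.** **This belongs in the SAP.** The article names no model for any outcome; ANOVA and χ² are mentioned for demographic and baseline data. Stratum adjustment is commonly left to the SAP, and the 30/30 layout would suit a within-stratum comparison. This stands in part: a SAP may contain the analysis, and the article does not show that exposure will in fact be ignored. But the article does fix the comparison and does list subgroups down to their cut-points, and both leave out the factor on which its title and post-trial condition depend. A SAP that analysed by exposure would be adding to that list.

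**The aim is broader than high exposure.** This is correct. The Background states it for exposed subway workers, and an overall comparison is a fair answer to that aim. A reader might infer that the primary analysis is invalid; it is not. What lacks support is the narrower claim made elsewhere in the article.

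**The power figures are assumptions.** This is also correct, which is why both readings and a range of SDs are shown.

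**Two stronger readings do not hold.** A reader might infer that leaving out the stratum inflates the variance, for example by 25% if the strata differ by 1 SD at baseline. The Abstract defines the primary outcomes as changes, and a constant baseline difference cancels from a change. Inflation would need the strata to differ in change, and the documents give no figure for that. A reader might also expect the band of over 10 years to be nearly empty, because the metro is fairly new. The Background says only that it has run for more than 10 years, with no upper limit and no distribution of service, so this cannot be concluded.

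**Conclusion.** The point holds as a mismatch between the claim and the stated analysis. Exposure is the stratification factor and the subject of the title, the intended conclusion and the post-trial condition, yet no stated comparison or subgroup yields the effect in highly exposed workers. This follows from the text alone.

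Its practical size depends on an SD that the article does not give. On either reading of the sample size, the overall test is a poor guide to a benefit confined to the highly exposed. The precision figures assume 20% dropout spread evenly over the four cells and a common SD. The finding does not extend to bias in the overall comparison, nor to what an unseen SAP may contain. The overlap at 6 years is a separate, minor error.

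**What to change.** Before unblinding, make these changes:

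1. Analyse the primary outcome with treatment, exposure stratum and treatment-by-exposure interaction.
2. Report the overall effect, the effect with 95% CI in each stratum, and the interaction.
3. State that the overall effect answers the Background's aim for exposed subway workers, and that any claim about highly exposed workers, including the condition in the Intervention section, rests on the high-stratum estimate.
4. Assign 6 years to one working-years band only.

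**Cost.** The change is to wording: exposure is already known for everyone and used in the randomization, so no new data are needed. The real price is statistical. The high-stratum interval is about 0.58/0.41 ≈ 1.4 times as wide as the overall one, its power may be only about 50% (Reading A), and the interaction test would be weak. A non-significant interaction should therefore not be read as evidence that the strata respond alike, and the high-stratum result should be judged by its interval.
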